**11.3 Post-trial access to effective products**

If this study, or other tenofovir studies, determines that tenofovir is safe and effective in preventing HIV infection, all HIV seronegative participants in this trial (both arms) will be provided with tenofovir at no cost for at least 1 year after trial termination. Tenofovir will be provided by Gilead Sciences, Inc. or purchased at cost by CDC.

**11.4 Counseling**

11.4.1 Pre-test counseling

Pre-test counseling will include an explanation of HIV infection and transmission, the meaning of HIV test results, risks associated with injection drug use, and an explanation of how to use condoms and how to use bleach to clean needles. Counseling messages will be tailored to each participant’s individual risk profile based on their sexual and drug use behaviors. Counselors will emphasize the unknown efficacy of tenofovir to prevent HIV infection and the double-blind, placebo controlled nature of the trial. Trained social workers and/or psychologists will perform all counseling.

11.4.2 Post-test counseling

Counseling will include goals, means, and strategies for behavioral risk reduction, maintenance of risk reduction, and explanation of risk reduction methods (e.g., condom use, cessation of drug use, cessation of needle sharing). Bleach and condoms will be provided free of charge.

Post-test counseling of HIV-infected participants will include an assessment of psychosocial needs, a discussion of living with HIV-infection and treatment, and issues related to discrimination. HIV transmission to partners will be discussed and strategies for behavioral change will be addressed (e.g., condom use, cessation of drug use, cessation of needle sharing).

**11.4.3 HIV risk reduction counseling**

All participants will receive HIV risk reduction counseling by trained study counselors at enrollment and each monthly visit. Trial participants will be informed of the risks associated with needle sharing, instructed on how to use bleach to clean needles, and provided with bleach free of charge. Participants will receive detailed information about methadone treatment programs available at the clinic. Participants will also be informed about sexual transmission of HIV, instructed in the use of condoms, and provided condoms free of charge. Participants will have an opportunity to ask questions about HIV infection and transmission at each visit.

**11.5 Informed consent**

Screening and enrollment informed consent forms were written in English then translated to Thai. In order to verify the translation, a translator not involved in the study, back translated the informed consents from Thai to English. Trained study staff will explain study procedures to the participants and discuss the advantages and disadvantages of participating. Staff will emphasize the voluntary and confidential character of the study, possible risks and benefits, alternatives to participation, and the participant’s right to withdraw from the study at any time.

**11.6 Participant confidentiality**

All study-related information will be treated as confidential. Study staff will be trained in procedures for maintaining participant confidentiality. A unique personal identification code will be used to identify questionnaires, laboratory specimens, and other materials. Records that contain names or other personal identifiers, such as locator forms and informed consent forms, will be stored in locked cabinets in areas with limited access. Electronic databases will be secured with password-protected access systems.

Participant’s study information will not be released without the written permission of the participant, except as necessary for study monitoring by: the BMA, the Thailand MOPH, the study monitor,the Thai FDA, Gilead Sciences, Inc., the U.S. CDC, the U.S. FDA, and/or other government and regulatory authorities.

**11.7 Compensation**

Participants will be compensated for their time, effort, and travel. Participants will receive350 baht (~8.75) for each monthly study visit. Participants on the DOT schedule who come all 7 days in a week will receive 350 baht for that week. In addition, participants who return to clinic for DOT will be reimbursed 70 baht for that visit. If tenofovir safety and efficacy is demonstrated, participants choosing to take tenofovir will receive 350 baht for 3-monthly visit but will not be compensated for daily or monthly visits.

**11.8 Management of pregnancy after study enrollment**

Women who become pregnant during the study will stop taking study drug and be withdrawn from the study. Prenatal care will not be provided by the study, but women will be assisted with antenatal care arrangements. In addition, women who become pregnant will be offered immediate voluntary HIV counseling and testing. Women testing positive for HIV will be referred and encouraged to participate in BMA ‘prevention of mother to child transmission’ services. After obtaining participant consent, clinic staff will review the medical record of delivery to assess maternal and newborn health. Pregnancy data and pregnancy outcomes will be reported to the Antiretroviral Pregnancy Registry ([contact], [contact], [contact]).

**11.9 General medical care**

The government of Thailand has a 30 baht (U.S. $0.75) program for emergency and general medical care. Patients pay 30 baht for each medical clinic or hospital visit. If a participant requires general medical care during the trial (e.g., broken arm, suture of laceration, pharyngitis), the sponsor will reimburse the participant the 30 baht cost of each medical visit.

**11.10 HIV-related care**

Thailand is expanding the government supported program to provide highly active antiretroviral therapy (HAART) and prophylaxis for opportunistic infections to all its citizens with a CD4 cell count < 200, an AIDS-defining illness, or prior antiretroviral therapy (ART). Trial participants who become HIV infected during the study will be referred to receive ART and prophylaxis for opportunistic infections (i.e., Standard Care) as described in the current *MOPH National Guidelines for Clinical Care of HIV-infected Adults and Children. 8th e*d. The sponsor will assure medical care for HIV-infected participants until these participants are offered Standard Care.

**11.11 Medical care for study drug associated adverse event**

Evaluation of adverse events will be provided with treatment if indicated and available at the study clinic. If not available, referral to an appropriate provider will be arranged. If a severe adverse event is caused by the study drug, the sponsor will ensure the participant receives appropriate medical care.

**11.12 Publication and presentation policy**

Publication of the results of this study will be governed by BTSG. Presentations, abstracts, and manuscripts will be submitted for review by BTSG, TUC, CDC, and Gilead Sciences, Inc., prior to submission.

**12. Clinical safety management and reporting**

**12.1 Definitions**

For the purposes of documentation and reporting of events related to the safety of participants receiving study medications in these trials, the International Conference on Harmonization (ICH) definitions and terminology will be used.

**12.2 Adverse event (AE)**

An AE is any unfavorable and unintended sign (e.g., an abnormal laboratory finding), symptom, or disease temporally associated with the use of an investigational product, whether or not considered related to the product.

An AE **does not** include:

- Diseases or conditions present or detected prior to taking study drug (i.e., pre-existing) which do not worsen during the trial
- Medical or surgical procedures (e.g., endoscopy, appendectomy); but the condition that leads to the procedure is an AE (e.g., bloody diarrhea, appendicitis)
- Situations where an untoward medical event has not occurred (e.g., hospitalization for elective procedure or for social reasons/convenience)
- Overdose of either study drug or concomitant medication without any signs, symptoms, or hospitalization

**12.3 Adverse drug reaction (ADR)**

An ADR is an AE where a causal relationship between the study medication (taken in doses normally used) and the adverse event is at least a reasonable possibility.

**12.4 Unexpected adverse drug reaction (ADR)**

An unexpected ADR is an ADR, the nature or severity of which is not consistent with the applicable product information (e.g., Investigator’s Brochure for an unapproved investigational medicinal product).

**12.5 Serious adverse event (SAE)**

An SAE is any untoward medical occurrence that at any dose of study medication may have resulted in:

- Death
- An immediate risk of death (i.e., “life threatening”)
- Admission to a hospital as an inpatient or prolongation of an existing hospitalization
- A persistent or significant disability or incapacity
- A congenital anomaly or birth defect
- A medical event that, based on clinical judgment, may jeopardize the patient and may require intervention to prevent one of the outcomes listed above

All Grade 4 severity events listed on the Gilead-modified NIAID Common Toxicity Tables for Adults (Appendix D) will be considered SAEs. Grade 3 severity events will be evaluated on a case-by-case basis and may be reported as SAEs if warranted in the clinical judgment of the evaluating physician. However, signs and symptoms will only be reported themselves as SAEs when a diagnosis of the event cannot be established and itself reported as an SAE.

**12.6 Evaluation of adverse events**

For every possible AE identified by interview, examination, or laboratory result, the study clinicians will evaluate and document on the appropriate study forms the following information:

- Nature: A description of the event or condition
- Severity: Graded in terms of interference with usual social and functional activities
- Mild: No or minimal interference with usual social and functional activities
- Moderate: Greater than minimal interference with usual social and functional activities
- Severe: inability to perform usual social and functional activities
- Life-threatening: inability to perform basic self-care functions; or medical or operative intervention indicated to prevent permanent impairment, persistent disability, or death
- Death
- Expectedness: In light of information in the Investigator’s Brochure
- Relationship: The relation between an adverse event and study drug may be characterized by grades of likeliness:
- Not related: clearly explained by another, documented cause
- Probably not related: more likely explained by another cause than by study drug
- Possibly related: study drug and other cause explain event equally well
- Probably related: more likely explained by study drug than any other cause
- Definitely related: Direct association with study drug
- Seriousness: Determination of whether it meets the definition of an SAE (listed above)
- Requirements for clinical management: Determine whether to suspend use of study medication, temporarily or permanently; conduct any indicated diagnostic or confirmatory testing; administer or refer for any indicated treatment; determination of need for unblinding to deliver effective care

**12.7.2 Routine periodic reporting**

Only routine reporting will be done for all ADRs, defined as AEs which may be related to study drug use (i.e., possibly, probably, or definitively related by above listed definitions) and that do not meet the criteria for SAE.

Routine reporting will consist of periodically providing a line listing of the events by type (e.g., lab toxicity or clinical event). These listings will be provided to the Gilead Sciences, Inc., U.S. CDC, and Institutional IRBs/ERCs for each annual continuation review; for each DSMB review; and on request from any regulatory agency involved in these trials.

**12.7.3 Documented on clinical forms but not otherwise reported**

All AEs will be documented on the appropriate clinical study forms. Those which are judged “unrelated” to study medication or “unclassifiable” (using the above listed criteria) will not be reported routinely, but the data will be available in the database should reporting of specific conditions be requested in future. Examples of such conditions are: accidental injuries (e.g., resulting from motor vehicle accidents or fires), diagnosed infectious diseases (e.g., malaria, urinary tract infection, STIs), progression of pre-existing conditions (e.g., cervical dysplasia).

**12.8 Clinical management of adverse events**

Adverse clinical events will be evaluated and managed at presentation by study physicians. The study physician will provide initial treatment and/or referral to an appropriate clinic or hospital. A decision will be made about the continuation of study product based on the toxicity grading scale (Appendix D) using the instructions outlined in section 12.8.1.

**12.8.1 Management of laboratory abnormality *(except serum creatinine elevation)* or clinical event**

**Grade 1 or 2:** Continue study medication at the discretion of the study physician.

**Grade 3 or 4:** May continue study medication, at the discretion of the study physician, for up to 3 days while values are confirmed.

**Confirmed grade 3:** If unrelated to study drug by above definitions, may continue dosing. If causal relationship to study drug possible by above definitions, withhold drug until toxicity returns to < grade 3 then retest to confirm participant is HIV negative then restart study drug. If toxicity > grade 3 recurs, permanently discontinue dosing and follow at scheduled study visits until toxicity resolves.

**Confirmed grade 4:** If unrelated to study drug by above definitions, may continue dosing. If causal relationship to study drug possible by above definitions, permanently discontinue study drug and follow at scheduled study visits until toxicity resolves. Do not rechallenge.

**12.8.2 Management of serum creatinine elevation**

The baseline serum creatinine is defined as the last value obtained from the laboratory prior to the administration of the first dose of study drug.

**All grades:** Continue study medication for up to 3 days whileserum creatinine value is confirmed.

**Confirmed grade 1:** Continue study medication at the discretion of the study physician and monitor as clinically indicated, generally weekly until serum creatinine value is within normal limits (Grade 0).

**Confirmed grade 2-4:** Permanently discontinue study drug and monitor as clinically indicated, generally weekly until serum creatinine value returns to within normal limits (Grade 0).

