**8.5 Participant withdrawal**

Participants may withdraw from the study for any reason at any time. The Principal Investigator also may withdraw participants from the study to protect the participant’s health and/or if the participant is unwilling or unable to comply with required study procedures. Such reasons include, but are not limited to, grade 4 creatinine elevation or grade 3 with recurrence, pregnancy, or the onset of health conditions that compromise study participation. Participants may also be withdrawn if the study sponsor, the BMA, the Royal Thai Government, or regulatory authorities terminate the study prior to its planned end date.

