**12.8.3 Management of creatinine clearance results**

Study medication will be adjusted according to modified Tenofovir dose adjustment for renal impairment guidelines (Gilead Sciences).10

|  | Creatinine Clearance | | |
| --- | --- | --- | --- |
|  | ≥50 mL/min | 30–49 mL/min | < 29 mL/min |
| Recommended Dosing Interval | Every 24 hours | Every 48 hours | Stop study medication |

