**Appendix D. Gilead Modified Common Toxicity Grading Scale – Adults**

IV = intravenous

|  | **Grade 1** | **Grade 2** | **Grade 3** | **Grade 4** |
| --- | --- | --- | --- | --- |
| **SERUM CHEMISTRY** | | | | |
| Creatinine (mg/dL) | An increase   0.5 from baseline | 2.1 – 3.0 | 3.1 – 6.0 | >6.0 |
| BUN (mg/dL) | 30 – 60 | 61 – 120 | 121 –240 | >240 |
| Magnesium (mEq/L) | 1.0 - <1.2 | 0.9 - <1.0 | - | - |
| Phosphorus (mg/dL) | 2.0 – 2.2 | 1.5 – 1.9 | 1.0 – 1.4 | <1.0 |
| Glucose (mg/dL) | 55 – 64 or  116 – 160 | 40 – 54 or  161 – 250 | 30 – 39 or  251 – 500 | <30 or  >500 |
| Bilirubin (mg/dL) | 1.3 – 1.8 | 1.9 – 3.0 | 3.1 – 6.0 | >6.0 |
| Amylase (U/L) | 97 – 131 | 132 – 175 | 176 – 439 | >440 |
| Lipase (U/L) | 154 – 210 | 211 – 279 | 280 – 699 | >699 |
| Creatine Kinase (U/L)  *(unrelated to trauma, exercise, or IM injection)*  Male  Female | 248 – 498  211 – 423 | 499 – 990  424 – 845 | 991 – 1980  846 – 1690 | >1980  >1690 |
| Cholesterol (mg/dL) | >ULN – 300 | 301-400 | 401-500 | >500 |
| Triglycerides (mg/dL) | - | 400 – 750 | 751 – 1200 | >1200 |
| Sodium (mEq/L) | 130 - <131 or  148 – 150 | 123 -129 or  151 – 157 | 116 -122 or  158 – 165 | <116 or  >165 |
| Potassium (mEq/L) | 3.0 – 3.3 or  5.6 – 6.0 | 2.5 – 2.9 or  6.1 – 6.5 | 2.0 – 2.4 or  6.6 – 7.0 | <2.0 or  >7.0 |
| Bicarbonate (mEq/L) | 16 - <17 | 11-15.9 | 8 – 10.9 | <8 |
| Calcium (mg/dL)  *(Ionized)*  Calcium (mg/dL)  *(corrected for albumin)* | 3.0 – 3.4 or  5.6 – 6.0  7.8 - <8.4 or  10.6 – 11.5 | 2.5 – 2.9 or  6.1 – 6.5  7.0 – 7.7 or  11.6 – 12.5 | 2.0 – 2.4 or  6.6 – 7.0  6.1 – 6.9 or  12.6 – 13.5 | <2 or  >7.0  <6.1 or  >13.5 |

|  | **Grade 1** | **Grade 2** | **Grade 3** | **Grade 4** |
| --- | --- | --- | --- | --- |
| **For patients with normal LFTs at baseline (< 2x ULN)** | | | | |
| AST or SGOT (U/L)  *Male*  Female | 45 – 90  43 – 85 | 91 – 180  86 – 170 | 181 – 360  171 – 340 | >360  >340 |
| ALT or SGPT (U/L)  *Male*  *Female* | 54 – 108  43 – 85 | 109 -215  86 – 170 | 216 – 430  171 – 340 | >430  >340 |
| Alkaline Phosphatase (U/L)  *Male 15-20 y*  *Male 21-59 y*  *Female 15-59 y* | 313 – 625  138 – 275  138 – 275 | 626 – 1250  276 – 550  276 – 550 | 1251 – 2500  551 – 1100  551 – 1100 | >2500  >1100  >1100 |
| **HEMATOLOGY** | | | | |
| Hemoglobin (g/dL) | 8.0 – 9.4 | 7.0 – 7.9 | 6.0 – 6.9 | <6.0 |
| Absolute Neutrophil Count (cells/mm3) | 1000 – 1500 | 750 – 999 | 500 – 749 | <500 |

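### Sections 12.8.2 and 12.8.3 can require incompatible actions on study drug for the same creatinine result, and the protocol does not say which prevails

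*Protocol*

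**What the plan says.** Four places in the protocol bear on study drug after an abnormal renal result.

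- **Section 12.8.2 (serum creatinine).** For confirmed grade 2 to 4: "Permanently discontinue study drug and monitor as clinically indicated", with checks about weekly until the value is normal again. No causality condition is attached and no restart is described. For confirmed grade 1: "Continue study medication at the discretion of the study physician and monitor as clinically indicated". Appendix D sets grades 2, 3 and 4 at "2.1 – 3.0 | 3.1 – 6.0 | >6.0" mg/dL; grade 1 is a rise of 0.5 mg/dL from baseline.
- **Section 12.8.3 (creatinine clearance).** "Study medication will be adjusted according to modified Tenofovir dose adjustment for renal impairment guidelines". The bands are "≥50 mL/min | 30–49 mL/min | < 29 mL/min", and the matching row reads "Recommended Dosing Interval | Every 24 hours | Every 48 hours | Stop study medication".
- **Section 12.8 (parent section).** It sends the decision on continuing study product to section 12.8.1, whose heading excludes serum creatinine elevation.
- **Section 8.5 (withdrawal).** Among its examples of reasons for which the investigator may withdraw a participant from the study is "grade 4 creatinine elevation or grade 3 with recurrence".

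Neither 12.8.2 nor 12.8.3 mentions the other, and no order of precedence is given elsewhere.

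**The concern.** Clearance is calculated from serum creatinine, so one laboratory result triggers both sections. If 12.8.2 ends dosing permanently while 12.8.3 continues it, at the same or a longer interval, a clinic cannot follow both.

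The trial runs at 17 clinics. Section 11.1 names renal injury among the reported risks of tenofovir, and section 7.1 makes grade 3 or 4 renal laboratory toxicity part of a primary safety endpoint. Three consequences follow if clinics resolve the conflict differently:

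- Study drug exposure and discontinuation counts would depend partly on which section a clinic follows.
- Section 14.5 lists failure to discontinue study medication when the protocol indicates it as a violation. A clinic that follows 12.8.3 at grade 2 would therefore be in breach of 12.8.2.
- A participant dosed every 48 hours takes 3 or 4 doses in seven days, so cannot meet the section 7.2 adherence measure of at least six daily doses out of seven.

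**Working it through.** The plan states no figure here to reproduce. The check applies the protocol's only clearance formula to its own creatinine grades and compares the two actions.

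**Inputs**
- Section 8.2, Cockcroft-Gault for men: clearance = (140 − age) × weight in kg / (72 × serum creatinine in mg/dL). It is given for eligibility; its use in 12.8.3 is an assumption.
- Section 8.2: ages 20 to 60. The protocol gives no body weights; 45 to 90 kg is assumed.
- Appendix D: the creatinine grades quoted above.
- Section 12.8.3: every 24 h at 50 mL/min or more, every 48 h at 30 to 49, stop below 29.

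**Worked cases (men)**

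| Age, weight | Creatinine | Grade and 12.8.2 action | Clearance (mL/min) | 12.8.3 action |
|---|---|---|---|---|
| 30 y, 60 kg | 2.1 | 2: permanent discontinuation | 110 × 60 / (72 × 2.1) = 43.7 | every 48 h |
| 30 y, 60 kg | 3.0 | 2: permanent discontinuation | 110 × 60 / (72 × 3.0) = 30.6 | every 48 h |
| 26 y, 70 kg | 2.1 | 2: permanent discontinuation | 114 × 70 / (72 × 2.1) = 52.8 | every 24 h |
| 26 y, 70 kg | 3.1 | 3: permanent discontinuation | 114 × 70 / (72 × 3.1) = 35.8 | every 48 h |
| 60 y, 50 kg | 2.0 | 1: continue at discretion | 80 × 50 / (72 × 2.0) = 27.8 | stop |

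The last case is a grade 1 result. Reading the 60 mL/min entry criterion as a minimum, this man's baseline creatinine is at most 80 × 50 / (72 × 60) = 0.93. A value of 2.0 is then a rise of at least 1.07, beyond the 0.5 for grade 1 and below the 2.1 for grade 2.

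**Sensitivity to weight.** For a man aged 30 at 2.1 mg/dL, clearance reaches 30 at 30 × 72 × 2.1 / 110 = 41.2 kg and 50 at 50 × 72 × 2.1 / 110 = 68.7 kg. From 41.2 kg upward, 12.8.3 keeps him on drug. Across ages and weights, the single value 2.1 mg/dL falls in all three 12.8.3 bands: 63.5 mL/min at 20 years and 80 kg, 42.3 at 60 years and 80 kg, 26.5 at 60 years and 50 kg.

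**Extent over the assumed range.** The grid covers men by single years of age, single kilograms and steps of 0.1 mg/dL. Values from 30 to just under 50 count as the middle band.
- Grade 2: 12.8.3 keeps drug going in about 75% of cells (64% every 48 h, 11% every 24 h).
- Grade 3: about 11% of cells, all every 48 h.
- Grade 4 (6.1 to 8 mg/dL): none. The highest clearance, at 20 years and 90 kg, is 120 × 90 / (72 × 6.1) = 24.6.

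These are shares of an unweighted grid, not expected proportions of participants.

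**Coverage of the bands.** In whole numbers, 29 mL/min lies below the middle band but not below 29, so it has no action. With decimals, 29 to under 30 and the interval between 49 and 50 are both unassigned.

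**The case against.** **The sections can be read in sequence.** Once 12.8.2 has permanently stopped the drug, no interval is left to adjust, and 12.8.3 governs those still dosing. The row label in 12.8.3 also calls its intervals recommended. This reading is reasonable and would remove the grade 2 and 3 conflict, but it is not written, and the sentence introducing the table is directive. It also leaves the grade 1 case open. There the conflict is milder: a physician who uses the discretion in 12.8.2 to stop satisfies both sections, but one section leaves open what the other fixes.

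**The table sign may be a slip.** Comparison signs are missing elsewhere in the text available here. If the final document prints at most 29 rather than below 29, the whole-number gap disappears. The main point does not depend on it.

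**Three stronger readings are tempting and not supported.**
- A reader might infer that 8.5 is a third conflicting rule, with withdrawal only at higher grades. It does not say so. It is permissive, its list is expressly open-ended, and it concerns leaving the study, not stopping drug. Section 12.8.1 shows that participants can stop drug and stay in follow-up. What remains is minor: recurrence after grade 3 suggests the withhold-and-restart pattern of 12.8.1, which excludes creatinine and sits awkwardly with permanent discontinuation.
- A reader might count as contradictory a fall in clearance without a graded creatinine rise. A man aged 58 at 50 kg going from 0.9 to 1.3 mg/dL moves from 82 × 50 / (72 × 0.9) = 63.3 to 82 × 50 / (72 × 1.3) = 43.8 mL/min. Section 12.8.2 is silent there and 12.8.3 acts alone, so nothing conflicts.
- A reader might infer that the renal safety results would change materially. The documents do not show this. Entry is restricted by clearance and renal history, clinics are blinded, analysis is by intention to treat, and grade 3 or 4 results are recorded whatever action follows. Action at grade 2 could still affect whether grade 3 is reached, but the number of participants concerned cannot be estimated from the protocol.

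**Conclusion.** The protocol contradicts itself. For many grade 2 and some grade 3 creatinine values, 12.8.2 ends study drug permanently while 12.8.3 continues it, and no precedence is stated. The parent section does not settle the matter, because it points to a section that excludes creatinine. At grade 4 the two sections agree on stopping over the range checked. The unassigned value of 29 mL/min and the recurrence wording in 8.5 are secondary.

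The sizes rest on two assumptions: that Cockcroft-Gault applies in 12.8.3, and body weights of 45 to 90 kg. Within that range the conflict does not hinge on a particular weight, although the 12.8.3 action does. The effect on trial results is unquantified. The case for correction is that clinics need one instruction on stopping study drug for a named toxicity. No view is taken on which clinical rule is right.

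**What to change.** Reconcile sections 12.8, 12.8.2 and 12.8.3 so that the protocol:

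- states which rule governs when creatinine grade and clearance point to different actions;
- names the clearance formula used in 12.8.3;
- assigns an action to every clearance value, including 29 mL/min and any decimals reported;
- directs creatinine results to the section that covers them.

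Align the creatinine wording in 8.5 with the outcome, keeping withdrawal from the study distinct from stopping study drug. The clinical leads decide the content of the reconciled rule.

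The cost is a protocol clarification and a memo to the clinics. No tests are added.
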